## Abstract

Technological innovation has revolutionized healthcare, particularly in neurological rehabilitation, where it has been used to address chronic conditions. Smart home and building automation (SH&BA) technologies offer promising solutions for managing chronic disabilities associated with such conditions. This single group, pre-post longitudinal pilot study, part of the H2020 HosmartAI project, aims to explore the integration of smart home technologies into neurorehabilitation. Eighty subjects will be enrolled from IRCCS San Camillo Hospital (Venice, Italy) and will receive rehabilitation treatment through virtual reality (VR) and robotics devices for 15 h per day, 5 days a week for 3 weeks in the HosmartAI Room (HR), equipped with SH&BA devices measuring the environment. The study seeks to optimize patient outcomes and refine rehabilitation practices. Findings will be disseminated through peer-reviewed publications and scientific meetings, contributing to advancements in neurological rehabilitation and guiding future research.

## 1. Introduction

Technological innovation has significantly reshaped various aspects of daily life, including healthcare, where advancements are continually improving patient care and outcomes. One notable area of progress is the integration of technology to enhance rehabilitation for individuals with neurological disorders [1,2]. This integration involves leveraging robotics, virtual reality devices, and sensor technologies to augment traditional rehabilitation methods and facilitate motor-function recovery [3]. These technologies not only promote patient engagement but also offer real-time monitoring capabilities, allowing for more personalized and effective treatment approaches [4].

Neurologic conditions often result in long-term disabilities, necessitating innovative solutions to enhance patient well-being and safety. Among these solutions, smart home and building automation systems (SH&BA) technologies have emerged as promising tools [5]. By monitoring patients’ health in real-time and providing data to healthcare professionals, smart homes enable proactive disease management, reducing the risk of exacerbations [6]. Moreover, these technologies promote patient independence and safety, aligning with the core objective of managing chronic conditions effectively [7]. Integrating smart homes within communities further enhances care continuity and enables timely interventions for older adults [8]. Recent technological advancements have opened new avenues for enhancing the effectiveness and accessibility of rehabilitation therapies for individuals with neurological disabilities. Among these innovations, the integration of SH&BA systems into neurorehabilitation therapies emerges as a promising opportunity to optimize rehabilitation outcomes. SH&BA systems, through the capability of monitoring, automation, and control of household devices and environments, provides an ideal context to extend the scope of rehabilitation therapies beyond traditional clinical settings. This innovative approach enables the creation of a safe, controlled, and personalized living environment that actively supports individuals through their rehabilitation journey, facilitating continuous practice and remote progress monitoring [6,7]. In this context, the integration of smart-home devices into rehabilitation therapies presents itself as a key strategy to improve effectiveness, efficiency, and overall patient experience during the neurological recovery process. This pilot study protocol aims to explore in detail the benefits and challenges of such integration, providing an empirical basis for its development and implementation in both clinical and home settings. Despite the promising results, to our best knowledge, the full potential of SH&BA systems in healthcare remains underexplored, with ongoing research efforts focused on uncovering new applications and optimizing existing systems.

Hence, the present single group-longitudinal pilot study, conducted within the H2020 “Hospital Smart development based on AI” (HosmartAI) project, aims to explore the impact of integrating smart-home sensors and actuators in a neurorehabilitation hospital by motor-recovery treatment uptake. It also seeks to assess the clinical efficacy and cost-effectiveness of motor treatment within a dedicated rehabilitation room (HosmartAI Room, HR) equipped with smart-home devices. Additionally, the study aims to investigate the usability and acceptability of such sensor integration among users and healthcare providers, with a view to improving the overall rehabilitation experience and optimizing patient outcomes. The possibility of applying motion detection and environmental control sensors in technological rehabilitation rooms could allow for the synchronization of environmental data with a patient’s clinical history to study functional recovery.

## 2. Materials and Methods

### 2.1. Study Setting and Design

To ensure the completeness and quality of reporting, we referred to the SPIRIT (Standard Protocol Items: Recommendations for Interventional Trials) [9] guidelines as well as Thabane and Lancaster’s [10] guidance on how to report protocols of pilot and feasibility trials. The protocol was registered in the ClinicalTrials.gov PRS database (Registration number: NCT06270420, https://clinicaltrials.gov/study/NCT06270420, accessed on 22 February 2024). This single group, pre-post longitudinal pilot study will be conducted within the HosmartAI research project (EU Horizon 2020, research and innovation program—grant agreement No 101016834). The trial will last twenty months and will be carried out at the San Camillo IRCCS Hospital (Venice, Italy), within which a smart rehabilitative room (HR) will be created. This room will feature rehabilitation devices complemented by smart-home sensors and actuators developed by VIMAR SpA (Marostica, Italy), all of which send data to a cloud system (Kloud) created by Khymeia Group (Padua, Italy). The purpose of this setup is to develop an innovative solution to monitor various activities that patients can perform autonomously or under therapists’ supervision. This solution aims to assist clinicians in monitoring patients within the hospital, identifying potential risks, and ensuring adherence to therapy protocols. Throughout the pilot phase, stakeholders involved will be closely observed using a persona-based approach, providing valuable insights into the behaviors of therapists and patients, thus enabling the analysis and exploration of the extension of active patient monitoring to the home environment.

Within the HR, various rehabilitative treatments will be conducted using different innovative devices. These will include the AMADEO^®^ system (Tyromotion GmbH, Graz, Austria), which is an upper limb rehabilitation robot enabling selective hand and finger movements. Additionally, the PABLO^®^ virtual reality rehabilitation system (Tyromotion GmbH), will provide immersive tasks with real-time biofeedback. The VRRS EVO^®^ (Virtual Reality Rehabilitation System, Khymeia Group Ltd., Padua, Italy) will offer virtual scenarios for kinematic tasks to be emulated by patient’s real arm movements while controlling a virtual object via a motion tracking system. Lastly, the OAK^®^ integrated virtual reality system (Khymeia Group Ltd.) will be used for fall risk assessment and prevention, enhancing balance and stability.

Additionally, the room will be equipped with smart-home sensors and actuators designed to gather environmental data and information, which can be conveniently accessed and managed by the physiotherapist through a digital interface. Developed by VIMAR SpA, these devices will encompass functions such as room occupancy monitoring (e.g., utilizing access control badges), tracking therapy dosage, detecting motion, monitoring temperature and light levels, and overseeing shutter position, as well as detecting falls. These smart-home devices aim to collect comprehensive data regarding various aspects of the environment within the healthcare facility. Physiotherapists will utilize a smartphone app (i.e., Vimar VIEW App, version 2.8.2 for Android and version 2.8.1 for iOS) to remotely oversee the HR’s environment and monitor patients’ activities. Moreover, the cloud system (i.e., Kloud, Khymeia Group Ltd.) will seamlessly integrate data coming from these devices, facilitating efficient data management and analysis to optimize patient care and rehabilitation outcomes.

### 2.2. Participants and Eligibility Criteria

The study will enroll 80 subjects among the patients hospitalized at the IRCCS San Camillo Hospital in Venice. Inclusion criteria for enrolment include an age greater than 18 years and a diagnosis of neurological pathology, such as ischemic and/or hemorrhagic stroke, Parkinson’s disease, multiple sclerosis, head trauma, brain tumor, ataxia, post-COVID syndrome, or peripheral neuropathy. Exclusion criteria include non-stabilized fractures, severe depression, significant visual and/or hearing impairments, dementia, uncontrolled epilepsy, severe neglect, and profound comprehension deficits that would hinder interactions with robotic and virtual reality devices.

### 2.3. Intervention

Subjects were enrolled among hospitalized patients based on the pre-defined inclusion criteria. The identification of eligible subjects was conducted through notification by the Clinical Research Unit at San Camillo Hospital. Subsequently, researchers from the HosmartAI project will enroll and evaluate (T0) the patients, after which they will commence their experimental treatment in the HR room, in addition to their regular daily conventional rehabilitation session. The experimental treatment will be tailored to the subjects’ therapeutic needs and will run for three weeks, comprising 15 one-hour sessions each, conducted five days a week. The specialized devices targeting balance, manual dexterity, and limb functionality, as described in the study setting section, will be utilized during these sessions. Pre-treatment (T0) and post-treatment (T1) assessments will be conducted using validated clinical scales and tests to determine therapy effects. Additionally, device-specific evaluation systems will be employed to assess treatment outcomes. A qualitative analysis will ascertain technology usability, acceptability, and user satisfaction. All assessments and treatments will be administered by qualified physiotherapists. Figure 1 illustrates the participants’ timeline.

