### 2.4. Outcome and Timelines

The primary aim of the study is to verify the productivity of the rehabilitation service at the IRCCS San Camillo Hospital following the sensorization of the HR with the smart-home system’s devices. Productivity outcomes will be measured through treatment performance, physiotherapists involvement, and adverse events. Assessments will be conducted monthly over a period of one year; the specifics are listed below.

Treatment Performance:Direct measurements of treatments provided in the HR, such as number of treatments provided per month; number of times accessed per month by system users (i.e., patients); number of therapy minutes provided per month and overall therapy duration.

Physiotherapist Involvement:The number of physiotherapists providing treatment relative to the number of patients will be quantified. This ratio (number of physiotherapists/number of patients), will reflect the allocation of staff resources during the study period.

Adverse Events:Measurement and recording of adverse events will involve number of falls occurring during the observation period within the HR.

The following secondary outcomes, changes in clinical parameters following therapies conducted in the HR, as well as satisfaction and user experience associated with the therapy, will also be assessed at baseline (T0) and at the end of the treatment, after 3 weeks (T1).

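### Secondary clinical outcomes: the T0-T1 change cannot show efficacy of HosmartAI Room therapy, because every patient also receives daily conventional rehabilitation and no comparison separates the two

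*Protocol article*

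**What the plan says.** Section 2.1 fixes the design: "This single group, pre-post longitudinal pilot study will be conducted within the HosmartAI research project". Under section 2.3 the HR course "will run for three weeks, comprising 15 one-hour sessions each, conducted five days a week", and patients "commence their experimental treatment in the HR room, in addition to their regular daily conventional rehabilitation session". The same section gives the purpose of the measurements before and after treatment: "assessments will be conducted using validated clinical scales and tests to determine therapy effects". The Introduction states the matching aim: "It also seeks to assess the clinical efficacy and cost-effectiveness of motor treatment within a dedicated rehabilitation room".

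Section 2.4 makes service productivity the primary aim and lists "changes in clinical parameters following therapies conducted in the HR" among the secondary outcomes. Section 2.6 compares T0 with T1 by a paired t-test or Wilcoxon test within each mode of delivery, where the mode depends on the physiotherapist/patient ratio. It then compares motor outcomes between treatment models with an independent-samples test. The Discussion presents cost savings with clinical outcomes not compromised as the novelty of the study, and later names the absence of control groups among the limitations of a pilot.

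**The concern.** Two treatments run side by side in the same three weeks, and one measurement interval covers both. A paired test on that interval asks whether scores moved. It does not ask which treatment moved them, or whether they would have moved without the HR.

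Conventional rehabilitation is given in order to improve function, so some background change is to be expected, and the documents do not say how much. Spontaneous recovery may add to it in some patients: section 2.2 admits inpatients with conditions "such as ischemic and/or hemorrhagic stroke, Parkinson’s disease, multiple sclerosis, head trauma" and others, and the listed criteria set no limit on time since onset. That part is inference, and it is less plausible for the progressive diagnoses on the list. The point does not depend on it, because the concurrent rehabilitation is stated outright.

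At stake is the clinical-efficacy aim, together with the Discussion's position that outcomes are maintained or improved under the new model. Both would rest on a change that inpatients on conventional rehabilitation might show anyway.

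**Working it through.** **Step 1: is there any comparison that isolates the HR?**

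- Paired tests (section 2.6): T0 against T1 in patients who all receive HR plus conventional care. There is no comparator.
- Between-model test (section 2.6): the models are tied to the physiotherapist/patient ratio, and all patients are treated in the HR. The test contrasts staffing arrangements within the HR, not HR against no HR.
- Pre-project data (section 3): mentioned for estimating savings. No comparison of motor scores with pre-project patients is described.

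None of these sets HR plus conventional care against conventional care alone.

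**Step 2: what the stated power refers to.** Inputs from section 2.5: n = 80, Cohen's d = 0.5, two-sided alpha = 0.05, power 0.99. For a paired t-test,

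power = 1 − F(t*; n−1, δ) + F(−t*; n−1, δ), with δ = d√n,

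where F is the noncentral t distribution function and t* the two-sided 5% critical value on n−1 degrees of freedom. Here δ = 0.5 × √80 = 4.47 on 79 degrees of freedom, and the power is 0.993. This reproduces the stated 0.99. With the Wilcoxon test the result is 0.991 or 0.984 (relative efficiency 0.955 or 0.864). An independent two-group t-test with 40 per group gives 0.598 and does not reproduce it. The advertised power is therefore consistent with a test of T0-T1 change against zero, whatever the cause of the change.

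**Step 3: how often that test is significant when the HR does nothing.** Set the HR effect to zero and let conventional care and any natural recovery shift scores by d SDs of the paired difference. The value of d is an assumption, shown as a range. The n = 40 column is also an assumption, since the article gives no delivery-mode sizes; it shows only the direction for smaller subgroups.

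| Assumed background d | P(p < 0.05), n = 80 | P(p < 0.05), n = 40 |
|---|---|---|
| 0 | 0.05 | 0.05 |
| 0.1 | 0.14 | 0.09 |
| 0.2 | 0.42 | 0.23 |
| 0.3 | 0.76 | 0.46 |
| 0.4 | 0.94 | 0.69 |
| 0.5 | 0.99 | 0.87 |

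Example: at d = 0.2 and n = 80, δ = 0.2 × √80 = 1.79, which gives 0.42.

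**The case against.** The strongest reply is that this is openly a single-group pilot, that its motor outcomes are secondary, and that the Discussion already concedes the absence of control groups and says the findings may inform larger trials. Much of this stands. The productivity aim is untouched, and the matter is one of interpretation of secondary outcomes. But the limitation is general: it does not mention the concurrent rehabilitation, and it does not withdraw the efficacy aim in the Introduction or the purpose given to the assessments in section 2.3.

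It can also be said that the phrase in section 2.4 about changes following HR therapies is only temporal, and that section 2.6 contains no rule declaring the HR effective. Both are fair. The causal reading comes from the Introduction and section 2.3, not from those sections.

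Three stronger readings are tempting and should not be made:

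- A reader might infer that a significant paired test is to be expected even if the HR adds nothing. The documents give no background change. At d = 0.1 the probability is 0.14, and section 2.6 tests within delivery modes, where numbers are smaller.
- A reader might infer that the motor change will be credited to the smart-home sensors. No section does this; sensorization is tied to productivity in section 2.4.
- A reader might try to work out the HR's share of total therapy time. The amount of conventional therapy is not stated, so no such share can be derived.

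**Conclusion.** The concern holds for the secondary clinical outcomes. As designed, the T0-T1 change measures change under combined conventional and HR rehabilitation, and no planned analysis can turn it into an effect of the HR. This follows from sections 2.1, 2.3 and 2.6 without any numerical assumption.

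Only the size is conditional. With no HR effect, the chance of a significant paired test at n = 80 runs from 0.14 to 0.99 as the assumed background change goes from 0.1 to 0.5 SD of the paired difference, and it is lower in smaller subgroups. The wording of the aim and of the assessments' purpose is wrong for this design and should be corrected. The defect does not reach the primary productivity outcomes.

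**What to change.** 1. In the Introduction and section 2.3, replace the references to clinical efficacy and therapy effects with *change during combined conventional and HR rehabilitation*.
2. State that no conclusion on HR efficacy will be drawn from T0-T1 change, and none that clinical outcomes were maintained because of the HR. Bring the Discussion into line.
3. Optionally, take conventional therapy minutes and time since onset from routine records and report them descriptively. They should not be presented as an adjustment that recovers an HR effect: every patient is scheduled for the same 15 HR sessions, so there is no planned contrast in HR exposure for a covariate model to use. A within-patient contrast of HR-trained against untrained domains is not a way round this either. Treatment is tailored to need, so the trained domain is likely to be the most impaired, and regression to the mean and greater room to improve would favour it.

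The cost is a few changes of wording and, if item 3 is adopted, two descriptive fields. No extra patients or visits are needed. The downside is a more modest claim. For scale, a concurrent conventional-care control with a between-group d of 0.5 would need 63 per arm for 80% power (normal approximation), that is 2 × 63 = 126 patients against the 80 planned. Rewording is therefore the proportionate step for this pilot.

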### 2.4. Outcome and Timelines

The primary aim of the study is to verify the productivity of the rehabilitation service at the IRCCS San Camillo Hospital following the sensorization of the HR with the smart-home system’s devices. Productivity outcomes will be measured through treatment performance, physiotherapists involvement, and adverse events. Assessments will be conducted monthly over a period of one year; the specifics are listed below.

Treatment Performance:Direct measurements of treatments provided in the HR, such as number of treatments provided per month; number of times accessed per month by system users (i.e., patients); number of therapy minutes provided per month and overall therapy duration.

Physiotherapist Involvement:The number of physiotherapists providing treatment relative to the number of patients will be quantified. This ratio (number of physiotherapists/number of patients), will reflect the allocation of staff resources during the study period.

Adverse Events:Measurement and recording of adverse events will involve number of falls occurring during the observation period within the HR.

The following secondary outcomes, changes in clinical parameters following therapies conducted in the HR, as well as satisfaction and user experience associated with the therapy, will also be assessed at baseline (T0) and at the end of the treatment, after 3 weeks (T1).

Changes in motor function:For change in upper limb function: The Box and Blocks Test [11] is a measurement of manual dexterity and gross motor skills. Participants move blocks from one side of a divided box to the other within one minute. The number of blocks transferred successfully serves as a measure of manual dexterity and motor function, with higher scores indicating better performance. The Nine Hole Pegboard Test (NHPT) [12] is a quantitative evaluation employed to assess finger dexterity and motor coordination. During the NHPT the participant is required to pick up nine pegs one at a time from a container, place them into nine holes on a pegboard, and then remove them again as quickly as possible. The time taken to complete the task is recorded, with a shorter completion time indicating better manual dexterity and hand function. The Reaching Performance Scale (RPS) [13] is a clinical assessment tool used to evaluate upper limb function, specifically reaching ability. The RPS consists of a set of six standardized tasks related to reaching for and grasping objects. The therapist is asked to decompose the reaching movement into its elements reaching a close (18 points) and far target (18 points), with each of the six movement components being scored from 0 to 3 and with a higher value indicating better performance.For lower limb function and walking: The Ten Meters Walk Test (10 mWT) [14] is used to assess walking speed in meters/second (m/s) over a short distance. Functional Ambulation Categories [5,15] is a 6-point assessment tool used to evaluate walking ability. FAC assesses the amount of human support a patient requires during walking, irrespective of their use of assistive devices. Scores range from 0 to 5, with higher scores indicating greater independence and lower levels of assistance required during walking.For trunk control and balance assessment: The Trunk Control Test [16] is a clinical assessment tool used to evaluate trunk control consisting of four items, each scored from 0 (unable to perform) to 25 (normal performance), with intermediate scores for partial performance. The total score is the sum of scores from all four tasks. The Berg Balance Scale (BBS) [17,18] is a 14-item objective measure designed to assess static balance and fall risk in adults. Each item is scored on a scale from 0 to 4, with a maximum total score of 56. Higher scores indicate better balance abilities.

Change in Health-related quality of Life (HRQoL) levels:The three-level version of EQ-5D (EQ-5D-3L) [19] is a standardized instrument for measuring health-related quality of life that consists of a descriptive system and a visual analogue scale (VAS). The descriptive system comprises five dimensions of health: mobility, self-care, usual activities, pain/discomfort, and anxiety/depression. Each dimension has three levels of severity: no problems, some problems, and extreme problems. The VAS records the respondent’s self-rated health on a scale from 0 (worst imaginable health state) to 100 (best imaginable health state).

Assessment of user experience and satisfaction:User satisfaction with the treatments provided in the HR will be assessed using the Short Form Patient Satisfaction Questionnaire (PSQ-18) [20], a self-reported 18-item questionnaire with a Likert scale ranging from 1 (strongly agree) to 6 (strongly disagree). It assesses patient satisfaction with healthcare services, investigating quality of care received, communication with healthcare providers, accessibility of services, and overall satisfaction with the healthcare experience.The System Usability Scale (SUS) [21] provides a quantitative measure of perceived user satisfaction and usability of a system, product, or a service. It consists of 10 items, each rated on a 5-point Likert scale ranging from “strongly agree” to “strongly disagree”. Scores range from 0 to 100, with higher scores indicating greater perceived usability. The User Experience Questionnaire (UEQ) [22] is an end-user questionnaire that measures a comprehensive impression of the product user experience, investigating the following dimensions: attractiveness, perspicuity, efficiency, dependability, stimulation, and novelty. It consists of 26 Likert-scale questions ranging from 1 to 7 points.

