### 2.6. Data Collection and Analysis Plan

Patient data, including clinical and demographic information, will be collected and inputted into treatment devices. A unified cloud platform will consolidate information from SH&BA devices and patient clinical data stored across devices. Data from HR sensors will gauge patient therapy adherence.

Descriptive analysis will be initially conducted on the enrolled subjects’ sample. For each demographic and clinical variable, we will consider the mean, standard deviation [23], absolute frequencies (n), and percentages (%). For each mode of clinical treatment delivery (i.e., depending on the physiotherapist/patient ratio), pre-treatment (T0) and post-treatment (T1) motor performance values will be compared using either Student’s t-test for paired data or the Wilcoxon test, depending on the data distribution, which will be assessed with the Kolmogorov–Smirnov test. To assess the presence of a statistically significant difference in motor recovery in relation to the type of treatment model, the motor outcomes of the patients will be compared by means of parametric or non-parametric independent sample comparison tests (i.e., Student’s t-test for independent data or the Mann–Whitney test), depending on the data distribution. To identify the patient profile that best fits each therapy model, regression models will be utilized, with the type of therapy model as the dependent variable, and assessment scales and anamnestic variables as predictor variables. To define the satisfaction, usability and technology acceptance and clinical profile of patients accessing technological therapy, tests for customer satisfaction will be utilized. The statistical significance is set at *p* < 0.05. Data analysis will be conducted using the free statistical software R Studio, version 4.0.3 [24].

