## 3. Discussion

This pilot study protocol outlines a structured approach to investigate the integration of SH&BA systems in neurorehabilitation, aiming to provide insights into the potential benefits and challenges of this innovative approach. Findings from this pilot study may inform the design of larger-scale trials and guide the implementation of smart-home technology in clinical practice, ultimately enhancing rehabilitation outcomes for individuals with neurological impairments.

With the ongoing advancements in digital healthcare, integrating into rehabilitation processes is crucial for enhancing patient care outcomes and management efficiency [6,7,8]. This study aims to combine technology with clinical requirements by sensorizing the environment. This enables the tracking of the number of eligible patients treated, the actual physiotherapy hours, and the ratio of physiotherapists to patients, all within existing financial constraints. By comparing pre-project data with the acquired results, potential savings of around 20–30% for the facility can be estimated. However, realizing the full potential of smart-home technologies in healthcare requires robust research methodologies and ethical considerations regarding data privacy. Continued research and development in these areas are essential to further optimize these technologies and maximize their benefits for patients and healthcare systems alike [25,26,27]. The study’s novelty lies in achieving cost savings while increasing productivity without compromising clinical outcomes. Personalized treatment remains paramount, ensuring patient-centric care through tailored device selection, exercise settings, and session management. Thus, even in the worst-case scenario, clinical outcomes are expected to be maintained, if not improved. Additionally, assessing device usability and patient satisfaction will validate the model’s viability. This project addresses the pressing need for increased therapy hours without escalating healthcare costs. Recruiting staff can be challenging, particularly in hard-to-reach areas, yet high-intensity rehabilitation centers, like San Camillo Hospital, must prioritize therapy hours. Balancing these needs requires economically feasible and qualitatively robust solutions, which this trial aims to provide.

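### Falls enter the primary outcome as a bare count: report them per patient-hour in the HR, overall and, descriptively, by physiotherapist/patient ratio

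*Protocol article*

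**What the plan says.** Section 2.4 of the protocol article sets the primary aim as the productivity of the rehabilitation service and states: "Productivity outcomes will be measured through treatment performance, physiotherapists involvement, and adverse events". The timing is given in the lead-in: "Assessments will be conducted monthly over a period of one year; the specifics are listed below". The adverse-event part reads: "Measurement and recording of adverse events will involve number of falls occurring during the observation period within the HR". The falls sentence itself speaks of the observation period; the monthly schedule comes from the lead-in.

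Two quantities that bear on fall risk are listed beside it as separate outcomes, with no link to falls. One is exposure: "number of therapy minutes provided per month and overall therapy duration". The other is staffing: "This ratio (number of physiotherapists/number of patients), will reflect the allocation of staff resources during the study period".

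Section 2.6 uses the staffing ratio to define modes of delivery, but only for motor scores: "For each mode of clinical treatment delivery (i.e., depending on the physiotherapist/patient ratio), pre-treatment (T0) and post-treatment (T1) motor performance values will be compared". The comparison between treatment models is likewise confined to these: "the motor outcomes of the patients will be compared by means of parametric or non-parametric independent sample comparison tests".

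The Discussion (section 3) presents more therapy hours without higher cost as the need that the project addresses, and claims: "The study’s novelty lies in achieving cost savings while increasing productivity without compromising clinical outcomes".

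**The concern.** A count of falls is readable as risk only if exposure is fixed or reported with it. Here exposure is one of the things under study: treatments and therapy minutes per month are primary measures, and the project wants them to rise. At unchanged risk, a busier room records more falls and a quieter room fewer. The adverse-event part of the primary outcome therefore moves with the treatment-performance part beside it.

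The second gap is the split. The organisational variable in this study is the number of physiotherapists relative to patients, and section 2.6 treats it as defining the delivery mode. Falls are the only adverse event that section 2.4 names, and a pooled total cannot show whether they cluster in one mode. If sessions and falls are not tagged with the ratio as they occur, that information may not be recoverable later.

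At stake is how a small number would be read. With this much exposure few falls are likely, and a report of zero or one fall, given without hours, invites a reassurance that the data cannot bear.

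**Working it through.** **The plan's own figure.** The only power statement is in section 2.5: d = 0.5, two-sided alpha 0.05, n = 80, power 0.99. A paired t-test with 79 degrees of freedom and noncentrality 0.5 x √80 = 4.47 gives 0.993, so the figure reproduces. It concerns a standardised mean change and says nothing about falls.

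**Exposure.**
- Patients: 80 (section 2.2). Sessions: 15 of one hour each (section 2.3). Full exposure: 80 x 15 = 1,200 patient-hours.
- Accrual: 4 patients a month for 20 months (section 2.5), so 4 x 15 = 60 h per month.
- One-year assessment window (section 2.4): 4 x 12 x 15 = 720 h.

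**Count against risk.** Expected falls = rate x hours. The documents give no fall rate, so 0.5 to 10 per 1,000 h is an assumed range. At 5 per 1,000 h:

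| Month | Hours | Rate per 1,000 h | Expected falls |
|---|---|---|---|
| As planned | 60 | 5 | 0.3 |
| Hours doubled, same risk | 120 | 5 | 0.6 |
| Hours halved, risk doubled | 30 | 10 | 0.3 |

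The count doubles with no change in risk in the second row, and hides a doubled risk in the third.

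**What zero falls would exclude.** The exact two-sided 95% Poisson upper limit for zero events is -ln(0.025) = 3.689.
- 1,200 h: 3.689 / 1.2 = 3.1 per 1,000 h.
- 720 h: 3.689 / 0.72 = 5.1 per 1,000 h.
- One mode with 600 h (assumed equal split of 1,200 h): 3.689 / 0.6 = 6.1 per 1,000 h.

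Zero is also a likely result. At 2 per 1,000 h, the chance of no falls is exp(-1.44) = 24% in 720 h and exp(-2.4) = 9% in 1,200 h.

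**What a split by mode could show.** Take two modes of 600 h each (assumed). Given N falls in all, the number in one mode is binomial with probability 1/2 if the rates are equal and 2/3 if one rate is double the other. With an exact test at 0.025 in each tail:

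| Lower rate per 1,000 h (assumed) | Power to detect a doubling |
|---|---|
| 0.5 | about 0% |
| 1 | 0.1% |
| 2 | 1% |
| 5 | 9% |
| 10 | 22% |

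For 80% power at a rate ratio of 2, the usual approximation is 4 x (1.96 + 0.84)² / (ln 2)², which comes to 66 falls after rounding up. Expected totals over 1,200 h at one common rate in the assumed range are 0.6 to 12.

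**The case against.** The strongest reply is that a condensed article may leave the choice of rate and interval to the full protocol or analysis plan, and that the overall denominator is already collected: therapy minutes per month, in the same room and on the same schedule. The second part stands for an overall rate, and it makes the change cheap. It does not cover a rate by mode, which needs falls and minutes both tagged with the ratio; the article does not say that they are. Nor does it say whether therapy minutes are patient, therapist or room minutes. If one therapist treats k patients together, patient-minutes are k times room-minutes, so the wrong choice distorts the rate most where staffing is thinnest. And section 2.4 does not leave the metric open: it names the count.

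It can also be said that planned exposure is nearly constant at about 60 h per month. On paper that is so, and the doubling above is an illustration, not a projection. But section 2.4 measures monthly volume because it may change.

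Three stronger readings are tempting, and the document does not support them.
- *Falls are the only outcome not examined by delivery mode.* Section 2.6 splits only motor performance. It states no such split for treatment performance, EQ-5D, PSQ-18, SUS or UEQ.
- *The Discussion claims that falls will not increase.* It speaks of clinical outcomes, while section 2.4 lists falls under productivity.
- *A rate by mode would show whether fewer therapists per patient cause falls.* It would not. Mode is not stated to be randomised, treatment is tailored to patients' needs (section 2.3), and section 2.6 itself looks for the patient profile that fits each model. Rates by mode would be confounded as well as imprecise.

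**Conclusion.** The point holds as one about how the outcome is defined. As a bare count, the adverse-event part of the primary outcome mixes risk with hours delivered and carries no information on the delivery mode in which falls happened. A rate per patient-hour repairs the first fault, and tagging by ratio repairs the second.

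The gain is in interpretation, not proof. Zero falls would leave an upper limit of about 3.1 per 1,000 h over 1,200 h, or about 5.1 over the roughly 720 h of the one-year window. Power to detect a doubled rate between two equal modes is at most about 22% over the assumed range. These figures assume that every patient completes 15 one-hour sessions, accrual is steady at four a month, falls follow a Poisson distribution and, for the power, each mode has 600 h. Lower attendance or an uneven split would generally widen the limits.

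**What to change.** In sections 2.4 and 2.6:
1. Define the outcome as falls per 1,000 patient-hours in the HR, with the number of falls, the patient-hours and an exact Poisson 95% interval, overall and by delivery mode.
2. Define the denominator as patient-minutes, not room or therapist minutes.
3. Tag each session's minutes and each fall with the physiotherapist/patient ratio in force, and each fall with the device in use.
4. Report zero falls with its upper limit, using the hours actually observed.
5. State that the rates by mode are descriptive, because modes are not stated to be randomised and the intervals will be wide, and that few or no falls is not evidence that lower staffing ratios are safe.

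The cost is some wording and two extra data fields (ratio and device). The safety statement will be less favourable than a bare zero, because its uncertainty will be visible.
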